### Qualitative research

We will conduct semi-structured interviews informed by a topic guide developed from the existing literature in conjunction with the research management committee which includes patient representatives [10].

With regard to recruitment, we will explore the reasons for participation and non-participation of patients and patients’ and clinicians’ acceptability of the trial. Non-participation can be related to how information is presented to the patient and the patient’s understanding of the information [11–13].

Participants will be divided into two groups according to whether they agreed or did not agree to be randomised to the trial. The interviews will explore patients’ perspectives of the treatment, their understanding of the two treatments, their reasons for taking part or refusing the trial, and their acceptability of randomisation between the procedures. We will recruit patients who refused randomisation, those who consented, and those who withdrew consent. Recruitment to the interviews will take place alongside recruitment to the trial.

### Sample size justification

The aim of this study is to assess the feasibility of performing a subsequent large definitive RCT on comparing videoendoscopic inguinal lymphadenectomy versus open radical inguinal lymphadenectomy in men with penile or urethral cancer. Therefore, sample size calculations are less relevant.

We aim to approach 170 eligible patients and ask for their consent to be randomised into the trial. We anticipate that the approximate recruitment (randomisation) rate will be 30%. As such, 170 patients would be sufficient to be able to estimate the consent rate to within ±7% through construction of 95% confidence interval for the recruitment rate. Under the assumption that the recruitment rate is approximately 30%, we anticipate that up to 50 patients will be randomised (1:1 VEIL: standard approach) to take part in the study. Sample sizes between 24 and 50 have been recommended to estimate the standard deviation required for a sample size calculation to allow us to design a large RCT aimed at evaluating the cost-effectiveness of videoendoscopic inguinal lymphadenectomy versus open radical inguinal lymphadenectomy in men with penile or urethral cancer requiring inguinal lymphadenectomy [14, 15].

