### Trial outcomes

The aim is to assess the feasibility of performing a RCT comparing videoendoscopic inguinal lymphadenectomy versus open radical inguinal lymphadenectomy in men with penile or urethral cancer requiring inguinal lymphadenectomy, and determine the design of a definitive RCT.

The primary outcome for this trial will be the feasibility of the RCT as assessed by:Ability to recruit patients across all participating sites (recruitment rate). We aim to recruit (randomise) > 30% (0.3) of eligible patients approached.Acceptability of the trial design and intervention to both patients and healthcare professionals through semi-structured interviews.

Recruitment rate will be monitored through screening and randomisation logs with the aim to recruit approximately three patients per month at all four sites.

There is currently no core outcome set for trials on patients with PeCa. Patient representatives and clinicians have identified complete removal of the cancer, different types of complications, successful completion of VEIL without requiring conversion to open lymphadenectomy, overall survival, health-related quality of life, length of hospital stay, return to normal activity, and the number of workdays lost (in those who work) as important outcome measures. These will be considered in this feasibility trial to help in the design of a definitive trial. We will measure these outcomes at 6 months after surgery.

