## Statistical analysis

### Quantitative analysis

Since this is a feasibility study, all analyses other than recruitment rate should be considered exploratory. Acceptability of the trial design to both patients and healthcare professionals will be assessed. Any exploratory comparisons will use means and standard deviations or medians and inter-quartile ranges for continuous variables, as appropriate, and frequency counts and percentages for categorical variables. The proportion of patients who consent to be randomised will be presented with a 95% confidence interval. For other outcomes, we will explore the mean difference in proportion (for binary outcomes) and mean or median difference (continuous outcomes) between the two groups and will be presented with associated 95% confidence intervals. No pre-specified formal comparisons between the groups will be made and no hypothesis tests will be carried out.

Other outcomes which may be considered are complete removal of the cancer, different types of complications, successful completion of VEIL without requiring conversion to open lymphadenectomy, overall survival, health-related quality of life, length of hospital stay, return to normal activity, and the number of workdays lost (in those who work). The randomisation stratification factors of centre and stage of cancer will be considered adjusting factors where appropriate. The results will inform us how sensitive the outcome measures are and, along with other information, will be used to determine the primary outcome of a subsequent large RCT. These results will inform the calculations for a sample size calculation for the most appropriate primary outcome. Any missing data mechanisms will be summarised from the VELRAD trial in preparation for a follow-on trial.

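### The recruitment figures do not agree: the target of more than 30% needs at least 52 of 170, the plan anticipates at most 50, and a true rate of 30% meets the target only 46% of the time

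*Protocol article*

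**What the plan says.** The Trial outcomes section of the protocol article makes recruitment rate one of two components of the primary feasibility outcome, beside acceptability assessed by interview, and gives it a numerical target: "We aim to recruit (randomise) > 30% (0.3) of eligible patients approached".

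The Sample size justification section gives the planned numbers:

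- Denominator: "We aim to approach 170 eligible patients and ask for their consent to be randomised into the trial".
- Assumed rate, in per cent: "We anticipate that the approximate recruitment (randomisation) rate will be 30".
- Precision: "170 patients would be sufficient to be able to estimate the consent rate to within ±7% through construction of 95% confidence interval".
- Expected yield, on the assumption of a rate of about 30%: "we anticipate that up to 50 patients will be randomised (1:1 VEIL: standard approach) to take part in the study".

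The Quantitative analysis section treats every analysis except recruitment rate as exploratory. For the rate itself it says "The proportion of patients who consent to be randomised will be presented with a 95% confidence interval". It adds that "No pre-specified formal comparisons between the groups will be made and no hypothesis tests will be carried out". The article does not say how the interval is to be read against the 30% target.

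**The concern.** The target, denominator, assumed rate and expected yield are all stated, and they do not agree. If 170 are approached and 50 randomised, the two planned numbers are reached and the recruitment target is missed.

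The target is also set at the rate the investigators expect. An observed proportion falls below its expected value about half the time, so a bare comparison with 30% says little about whether a definitive trial is feasible.

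This matters because recruitment rate is the only analysis not labelled exploratory. The article's own justification for a feasibility study is that the one earlier attempt at this comparison could not randomise because of patient preference. A result such as 50 or 51 of 170 is among the most likely under the plan's assumptions, and the article leaves unclear whether it would count as meeting the aim.

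**Working it through.** **Inputs.** Target: more than 0.30 of those approached (Trial outcomes). Number approached n = 170, anticipated rate p = 0.30, precision ±7 points at 95%, yield up to 50 (all from Sample size justification).

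**1. The plan's own figures.** Normal-approximation half-width = 1.96 × √(p(1−p)/n) = 1.96 × √(0.30 × 0.70/170) = 0.0689, or 6.9 points. This reproduces the stated ±7. Expected number randomised = 170 × 0.30 = 51, so 50 is this figure rounded down.

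**2. Count needed for the target.**

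| Randomised of 170 | Rate | More than 30%? |
|---|---|---|
| 50 | 29.4% | no |
| 51 | 30.0% exactly | no |
| 52 | 30.6% | yes |

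The target needs at least 52, two more than the upper figure anticipated.

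**3. Chance of meeting the target with 170 approached.** X is the number randomised, X ~ Binomial(170, p).

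| True rate p | P(X ≥ 52), target > 30% | P(X ≥ 51), target ≥ 30% |
|---|---|---|
| 0.25 | 0.058 | 0.080 |
| 0.30 | 0.462 | 0.529 |
| 0.32 | 0.680 | 0.737 |
| 0.33 | 0.772 | 0.819 |
| 0.35 | 0.902 | 0.927 |
| 0.40 | 0.996 | 0.997 |

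Solving P(X ≥ 52) = 0.80 gives p = 0.3335, about 33.3%. Solving for 0.90 gives p = 0.350.

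**4. Range of the yield.** The 2.5th and 97.5th percentiles of Binomial(170, 0.30) are 40 and 63. P(X ≥ 51) = 0.529, so at the assumed rate the yield is more likely than not to exceed 50. As an upper figure for what is anticipated, 50 is wrong even without the target.

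**5. If 50 were a cap (not stated in the article).** Recruitment would end at the 50th randomisation. The target is then met when at most 166 have been approached: 50/166 = 30.1%, while 50/167 = 29.9%. At p = 0.30 this has probability P(Binomial(166, 0.30) ≥ 50) = 0.516. The number approached would be about 50/p, and the half-width 1.96 × √(p(1−p)/(50/p)):

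| Rate p | Approached | Half-width |
|---|---|---|
| 0.40 | 125 | 8.6 points |
| 0.50 | 100 | 9.8 points |

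With all 170 approached, the half-width at p = 0.40 is 1.96 × √(0.40 × 0.60/170) = 7.4 points.

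**6. What the planned interval shows.** Normal-approximation 95% limits are 22.6% to 36.3% for 50/170 and 23.7% to 37.5% for 52/170. The two intervals are almost the same, although only the second point estimate meets the target.

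**The case against.** The strongest reply is that this is loose wording and not a design fault. The sentence about 50 patients is an expectation, conditional on an approximate rate, and 50 is 51 rounded. The target is phrased as an aim, no test is planned, and nothing says that 29.4% means not feasible. Feasibility also rests on acceptability. On this view the 46% only restates that an estimate falls on either side of its expected value about equally often.

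Much of this stands, and it rules out two stronger readings:

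- A reader might infer that the target cannot be met. That would require both a firm ceiling of 50 and a fixed 170 approached. The article states no ceiling and no rule to stop at 50. With no ceiling, 52 or more of 170 meets the target. With a stop at the 50th randomisation, the denominator shrinks, and the chance at a true 30% is 0.52, slightly higher than without it.
- A reader might infer that the ±7 precision is lost when consent is good. That too depends on a stop the article does not state. With 170 approached, the half-width at a 40% rate is 7.4 points.

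Detailed progression rules may sit in the full protocol or analysis plan, so their absence from an article is not the complaint.

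What the reply does not remove is the mismatch in figures the article does print. An upper figure of 50 from 170 falls below a target of more than 30%, and the target coincides with the assumed rate. That near coin-toss behaviour is the reason not to judge the aim on a bare point estimate.

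**Conclusion.** The point holds as an inconsistency between the Trial outcomes and Sample size justification sections. The target needs 52 of 170, and the plan anticipates no more than 50 (29.4%). A trial that performs as assumed meets its target with probability 0.46, or 0.53 if the target is read as at least 30%. The true rate must be about 33.3% for an 80% chance.

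These probabilities assume that 170 are approached, that patients decide independently with a common probability, and that the aim is judged on the observed proportion alone. The precision statement itself is correct for 170 approached. The documents do not show that the target is unattainable. They show that it is misaligned with the planned numbers, and that a likely result such as 50 or 51 of 170 would be recorded as falling short although its interval is compatible with rates well above 30%.

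**What to change.** 1. In Sample size justification, replace the upper figure of 50 with an expected value and range: about 51 randomised (95% range 40 to 63).
2. State that all 170 are approached whatever the running count, so that the ±7 precision holds. If 50 is in fact a cap, say so, restate the target to match (50 of 170 is 29.4%), and give the precision for the number that would then be approached.
3. State whether the target is more than 30% or at least 30%.
4. Judge the target with the 95% confidence interval already planned, not the bare proportion. The sponsor should choose the minimum acceptable rate and name the interval method. As an illustration only, requiring the lower limit to exceed 20% needs 45 of 170 with the Wilson interval (met 86% of the time at a true 30% and 2.5% at a true 20%). With the normal approximation, 45 of 170 has a lower limit of 19.8%, so 46 are needed (met 82% of the time at a true 30%). The 20% figure is not in the article and is not a recommendation.

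The cost is a few sentences in two sections and no extra patients, provided that 50 is not a cap. The downside is that the stated target may look slightly less ambitious.

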### Patient and public involvement

Our oversight committee comprises of an external Consultant Urologist and a designated patient representative. The committee will be consulted throughout the trial and have access to relevant trial documents.

## Statistical analysis

### Quantitative analysis

Since this is a feasibility study, all analyses other than recruitment rate should be considered exploratory. Acceptability of the trial design to both patients and healthcare professionals will be assessed. Any exploratory comparisons will use means and standard deviations or medians and inter-quartile ranges for continuous variables, as appropriate, and frequency counts and percentages for categorical variables. The proportion of patients who consent to be randomised will be presented with a 95% confidence interval. For other outcomes, we will explore the mean difference in proportion (for binary outcomes) and mean or median difference (continuous outcomes) between the two groups and will be presented with associated 95% confidence intervals. No pre-specified formal comparisons between the groups will be made and no hypothesis tests will be carried out.

Other outcomes which may be considered are complete removal of the cancer, different types of complications, successful completion of VEIL without requiring conversion to open lymphadenectomy, overall survival, health-related quality of life, length of hospital stay, return to normal activity, and the number of workdays lost (in those who work). The randomisation stratification factors of centre and stage of cancer will be considered adjusting factors where appropriate. The results will inform us how sensitive the outcome measures are and, along with other information, will be used to determine the primary outcome of a subsequent large RCT. These results will inform the calculations for a sample size calculation for the most appropriate primary outcome. Any missing data mechanisms will be summarised from the VELRAD trial in preparation for a follow-on trial.

### Qualitative analysis

Interviews will be transcribed verbatim and managed and coded using NVivo Computer Assisted Qualitative Data Analysis Software (i.e. NVivo). Braun and Clarke’s model of thematic analysis with a six-phase approach will be used to generate, review, and define themes within the interview transcripts [16]. The transcripts will be analysed by two researchers. The first researcher will fully code and analyse all transcripts. A sample of these will then be analysed by a second researcher. Themes will be double-checked by the second researcher, and any disagreements will be discussed and resolved within the qualitative research team. Information gained from the process evaluation will be used to inform the development of the protocol for a definitive trial.

### Health economic analysis

We will undertake a feasibility study for an economic evaluation to compare VEIL with open inguinal lymphadenectomy in men with penile or urethral cancer. The feasibility study will be used to plan the evaluation within a subsequent trial, which will aim to estimate the incremental cost of the VEIL and the potential benefit in economic terms from the NHS perspective and personal social services (PSS) perspective versus open inguinal radical lymphadenectomy in men with penile or urethral cancer. We will also explore the feasibility of collecting data to assess the costs for patients and families from a broader perspective.

With the available data, we will perform a preliminary analysis of the cost-utility of VEIL with open inguinal lymphadenectomy in men with penile or urethral cancer to inform a future trial.

## Discussion

Open radical inguinal lymphadenectomy is a procedure with a high short-term and long-term morbidity. Consultation with a Penile Cancer Patient Support group at the host institution indicated that for 9/9 (100%) of patients completing the questionnaire, complications of the procedure were one of the top three most important factors they considered in relation to undergoing lymphadenectomy. The proposed comparison of methods of lymphadenectomy (videoendoscopic inguinal lymphadenectomy versus open inguinal lymphadenectomy) was discussed in the PeCa patient support group in April 2018, and most patients felt this was an important topic to be researched.

Between 20 and 60% of patients undergoing radical lymphadenectomy have one or more of the following complications: lymphoedema (lower limb or genital), lymphocele, wound infection, wound dehiscence, flap necrosis, recurrent cellulitis or deep vein thrombosis [6, 8, 17]. Videoendoscopic inguinal lymphadenectomy may decrease these complications compared to open radical lymphadenectomy and provide equivalent short-term oncological outcomes. However, this is based on non-randomised studies and the long-term oncological outcomes are unknown [18]. There is also concern regarding the higher risk of lymphocele, which is usually asymptomatic, but can be painful and require treatment in about 4 to 7% of people [6, 19]. In the only attempted RCT comparing VEIL versus open radical inguinal lymphadenectomy, it was difficult to recruit because of patient preference for VEIL in the USA. The majority of patients in this trial were also patients diagnosed with melanoma [9]. In addition, non-participation can be related to how information pertaining to the clinical trial is presented to the patient, and the patient’s understanding of the information [11–13]. There are currently no other published RCTs comparing VEIL versus open radical inguinal lymphadenectomy.

We searched the ClinicalTrials.gov and WHO ICTRP (World Health Organization International Clinical Trials Registry Platform). There is only one ongoing RCT involving patients with PeCa undergoing lymphadenectomy [20]. This trial (InPACT) is being conducted in the UK as well as North America and other South American centres to investigate the role of neoadjuvant treatment in large inguinal nodes along with inguinal lymphadenectomy and the role of pelvic node dissection in patients with PeCa [20]. This trial is recruiting patients with larger volume nodal disease requiring neoadjuvant chemo-radiation and will therefore not compete with the current trial which is for non-palpable or small volume nodes. There is currently no ongoing RCT comparing VEIL versus open radical inguinal lymphadenectomy in patients with PeCa worldwide.

## Data Availability

Data sharing is not applicable to this article as no datasets were generated or analysed during the current study.
